### Setting

#### Web-Based Consent, Self-Assessment, and Automated Eligibility Determination

Figure 2 shows the flowchart of participants through different components of the study. It includes the enrollment process, followed by randomization, mailing of the medication, and follow-up surveys completed at various time points.

Interested individuals will visit the study website and read a brief description of the study purpose, its procedures, and treatments provided. Those interested in participating will read the study information and consent form and provide their consent by clicking “yes” on the study website; they may also indicate whether they would like to be contacted for future studies. Individuals are permitted to participate in the study even if they do not give consent to be contacted for future studies. After completing the consent form, participants will complete the baseline survey, which will take approximately 20 minutes. The baseline questionnaire collects information on demographics, socioeconomic factors, education, ethnicity, smoking habits (cigarettes smoked per day, duration of daily smoking, and when participants first began smoking), importance and confidence to quit, substance and alcohol usage, concurrent usage of other medication(s), and any psychiatric comorbidities (ie, depression, anxiety, and schizophrenia).

In addition, if eligible, participants will be asked if they consent to provide a saliva sample for the genetic testing component of the study. If they agree to enroll in this substudy, they will complete the Big Five Aspect Scale personality test online through the study website, which will take approximately 10-15 minutes. Big Five Aspect Scale is a self-reported public domain test, which assesses the big 5 personality traits by asking 100 questions answered on a 5-point scale ranging from “strongly disagree” to “strongly agree” [14]. Individuals will be permitted to take part in the efficacy study even if they do not consent to participation in the genetics substudy. The questionnaires used have been published previously and include the Fagerstrom test for nicotine dependence [15], the BFAs for accessing the big 5 personality traits—extraversion, neuroticism, conscientiousness, agreeableness, and openness to experience [14]—and Patient Health Questionnaire for the evaluation of depression [16]. These questionnaires have been widely used in clinical studies, involving smoking, and extensively validated [14-16].

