#### Randomization

Eligible participants will be randomly assigned to one of the 2 study arms (varenicline or bupropion). Permuted block randomization in a 1:1 ratio in blocks of 100 will be employed. The randomization process will be computerized. Owing to the large proposed sample size in this study, there will be no stratification or minimization.

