### Data Analysis

Analysis of study results will be conducted using the intention-to-treat analysis, wherein all participants who are randomized to a treatment arm and receive their assigned medication are included in the final analysis whether they complete the study or respond to follow-up surveys at study end points. This method will be used to avoid any bias that can potentially arise because of crossover and dropouts, affecting the initial random assignment to treatment groups. Participants who are lost to follow-up or do not provide a saliva sample for the COT confirmation of abstinence will be considered as smokers according to recommendations by the Society for Research on Nicotine and Tobacco’s subcommittee on Biochemical Verification (2002) [21].

The baseline characteristics will be analyzed and compared between intervention groups using the Student’s *t* test for continuous variables and cross-tabs chi-square analysis for all categorical variables. Any characteristics that differ significantly across our 2 study groups will be included as covariates in all subsequent analyses. The effect of intervention over time will be evaluated using the longitudinal logistic regression analysis with abstinence as the dependent variable and treatment condition along with other baseline characteristics as independent predictors. We will construct a longitudinal generalized estimating equations (GEE) model for each binary outcome. GEE is a suitable analysis method because it accommodates for the statistical dependence among repeated observations within subjects. Because our primary outcome is abstinence from smoking (Yes or No) at each follow-up time point, GEE is appropriate because it allows for the estimation of population-averaged effects while accounting for the dependencies among the repeated measures. The data analysis for this study will be overseen by the principal investigator in consultation with the Biostatistical Consulting Service at CAMH.

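### Covariates for all analyses are chosen by between-arm significance tests at baseline, which do not identify predictors of abstinence and leave the adjusted model undetermined until baseline data by arm are seen

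*Protocol article*

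**What the plan says.** All the statements are in the protocol article.

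- Data Analysis: the arms are compared at baseline "using the Student’s *t* test for continuous variables and cross-tabs chi-square analysis for all categorical variables". No threshold and no list of variables is given. The rule follows: "Any characteristics that differ significantly across our 2 study groups will be included as covariates in all subsequent analyses".
- Data Analysis, next sentence: the longitudinal logistic (GEE) model has "treatment condition along with other baseline characteristics as independent predictors". None is named.
- Data Analysis, analysis set: "all participants who are randomized to a treatment arm and receive their assigned medication are included in the final analysis".
- Web-Based Consent, Self-Assessment, and Automated Eligibility Determination: the baseline survey covers, among other things, "smoking habits (cigarettes smoked per day, duration of daily smoking, and when participants first began smoking), importance and confidence to quit". It also includes the "Fagerstrom test for nicotine dependence" and a depression questionnaire.
- Randomization: "Permuted block randomization in a 1:1 ratio in blocks of 100 will be employed", and "there will be no stratification or minimization". There are therefore no design factors that would fix an adjustment set.

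**The concern.** A covariate earns its place in the model of a randomised comparison by predicting the outcome. The between-arm p value answers a different question: how unusual the observed imbalance is if allocation alone produced it. A rule built on that p value can admit variables unrelated to quitting and pass over variables that matter.

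Two things are at stake. First, the rule governs every later analysis, including the primary 26-week comparison, so the adjusted model cannot be written down until baseline data by arm have been inspected. An odds ratio is also conditional on the covariates in its model, so the quantity estimated changes with whatever happens to be selected. Second, whatever power could be gained by adjusting for known predictors is left to accident.

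**Working it through.** The plan attaches no figure to this rule, so there is none to reproduce. The check has four steps.

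**1. Chance that one given variable is selected.** Assume a threshold of .05 for the baseline tests; the article states none. With a randomised set, each test is significant with probability 0.05 whatever the variable's link to abstinence. The rule therefore passes over a given predictor with probability 1 − 0.05 = 0.95. Simulated selection of a prognostic variable was 4.6% to 5.4%.

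**2. Chance that something enters by luck.** For k independent characteristics, the expected number selected is 0.05k, and P(at least one) = 1 − 0.95^k. Both k and independence are assumptions.

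| k | Expected number | P(at least one) |
|---|---|---|
| 10 | 0.50 | 40% |
| 15 | 0.75 | 54% |
| 20 | 1.00 | 64% |
| 30 | 1.50 | 79% |

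**3. Consequence for the treatment test.** The simulation used 500 per arm with abstinence of 20% versus 15% (both from Sample Size), or 15% in both arms for the null case. It had 15 independent covariates, one of them prognostic, with 4,000 replicates and two-sided .05. The prognostic strengths are assumed, because the article gives none. The model was a logistic regression at one time point, not the full GEE, and no selection after randomisation was built in.

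| Assumed OR per SD | Power, unadjusted | Power, selected by baseline test | Power, predictor fixed in advance |
|---|---|---|---|
| 1.65 | 55.6% | 55.7% | 56.8% |
| 2.2 | 54.2% | 54.5% | 57.9% |
| 2.7 | 54.9% | 55.4% | 60.3% |

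The gains of the fixed predictor over the selected model are 56.8 − 55.7 = 1.1, 57.9 − 54.5 = 3.4 and 60.3 − 55.4 = 4.9 points. The Monte Carlo standard error of each power is about 0.8 point. The selected model performs almost exactly like the unadjusted one. Type I error was about 4.5% to 5.3% under all three approaches.

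The unadjusted power agrees with the two-proportion formula (54.8%) and not with the 80% in Sample Size. That is a separate matter and this point does not rest on it.

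**4. The two sentences side by side.** The rule adds variables that differ significantly. The next sentence has baseline characteristics in the model but does not say whether these are the selected ones or additional ones. On the first reading, chance largely decides the model. On the second, predictors may be present, but which ones is not stated. On neither reading is the adjusted model determined in advance.

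**The case against.** The strongest reply is that the plan does not leave predictors out. A reader might infer from the rule that dependence, cigarettes per day or confidence to quit will be missing from the model. The documents do not support that: the next sentence leaves room for them. An unnamed covariate list is also something a condensed article may leave to a fuller document, so the absence of names is not in itself a fault. This stands, and it limits the point to the stated rule.

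A reader might also infer that every significant baseline difference in this trial must be a chance finding. That holds for all randomised participants. The analysis set, however, is restricted to those who received the assigned drug, after open allocation (Blinding) and a prescriber's decision whether to sign (Patient Visit to a Licensed Practitioner). A difference in that set may be systematic. This qualifies the 5% figure but does not rescue the rule: a significance filter on measured variables does not reliably repair such selection, and a non-significant test does not exclude it.

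Three further limits stand:

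- The rule looks at baseline data, not outcomes, so it does not by itself allow outcome-driven choice of covariates.
- A 40% to 79% chance of an extra covariate is not bias. The characteristics are also unlikely to be independent; cigarettes per day and the dependence score are an obvious pair.
- Prespecified adjustment should not be recommended as reducing the standard error of the log odds ratio. In a second simulation (1,500 replicates, same assumed strengths) the mean standard error rose from 0.168–0.169 unadjusted to 0.172, 0.176 and 0.180 adjusted. The gain in power comes from a larger conditional odds ratio.

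**Conclusion.** The point holds as a criticism of the selection rule. The rule is stated outright, applies to every analysis, and ties adjustment to a quantity that carries no information on prognosis. It neither secures the inclusion of useful covariates nor lets the adjusted model be known before baseline data by arm are seen.

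The practical size is modest. Under the assumed strengths, a fixed predictor would gain about 1 to 5 points of power over the rule; at the weakest strength the gain is close to the simulation error. No inflation of type I error was found, although the simulation covers pure randomisation only. The 5% and the 40% to 79% rest on an assumed .05 threshold, and the latter also on an assumed count and independence. The stronger conclusions, that strong predictors are excluded or that the test of treatment is invalid, are not supported. The change is still worth making, because a better rule is available from data already in hand.

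**What to change.** Delete the significance-test rule. Fix a short list of prognostic covariates collected at baseline, for example Fagerstrom score, cigarettes per day, confidence to quit, Patient Health Questionnaire score and age. Keep them in the GEE/logistic model whatever the observed balance. State that this list is the whole of the baseline adjustment, so that the next sentence no longer leaves it open. Present baseline characteristics descriptively by arm, without p values.

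Enrolment is complete and the Results section says analysis is underway, so a list written now cannot simply be called prespecified. Choose it on prognostic grounds without reference to outcome results by arm, disclose the date it was set, and report the unadjusted result alongside. If the existing rule has already been applied, show that result as well.

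The cost is a sentence or two in Data Analysis and one extra reported estimate. No new data are needed. The list does not cure any selection arising between randomisation and receipt of the drug.

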## Results

The project was funded in 2014 and enrollment was completed in January 2017. Data analysis is currently underway and the first results are expected to be submitted for publication in October 2018.

## Discussion

The proposed trial on providing free medication mailed to smokers is expected to be cost effective and will be useful for policy makers to consider as part of a comprehensive tobacco control strategy. This can help reduce the prevalence of smoking and its related costs to our health care system and the overall economy. With the knowledge gained, the method can be modified according to the peculiarities of other health care jurisdictions to impact the smoking prevalence in those areas as well.

## Appendix

Multimedia Appendix 1 Example emails of MATCH weekly motivational messages.

## Abbreviations

CAMH: Centre for Addiction and Mental Health
CAR: continuous abstinence rate
CONSORT: Consolidated Standards of Reporting Trials
COT: cotinine
GEE: generalized estimating equation
MATCH: Medication Aids for Tobacco Cessation Health
OR: odds ratio
PPA: point prevalence abstinence
RCT: randomized controlled trial
REB: Research Ethics Board
